## Methods

### Participants

The G*Power statistical software, version 3.1.9.7, developed in Heinrich Heine University Düsseldorf, was used to calculate the sample size using the bone biomarker CTx-I; a recommended number of 36 women would be required for the study. However, 40 women aged >60 years will be recruited for each of the 4 groups to allow for a possible dropout rate of 10%. The test groups will receive the synbiotic food supplementation and exercise program (10,000 steps brisk walking per day required), whereas the control group will receive a placebo and no exercise; however, dietary intake and exercise will be monitored by a 3-day diet diary and the International Physical Activity Questionnaire. All study participants will read the information sheet, and signed and written consent forms will be obtained from them.

### Inclusion Criteria

The inclusion criteria include a confirmed menopause diagnosis (by an initial blood test—baseline screening—that includes checking the levels of follicle-stimulating hormone [≥30 mIU/mL] and estrogen) of at least five years based on no menstruation and the BMI of all participants will be between 17 and 35 kg/m².

### Exclusion Criteria

The following criteria are to be confirmed by medical history or measurements:

Use of HRTBiphosphonates in the past 6 monthsCurrently on estrogen, tamoxifen, aromatase inhibitors, or other antiresorptive or anabolic treatments of osteoporosisA liver function test or creatinine level above the normal range, or any other history suggesting liver or kidney disease to be confirmed by baseline screeningIncidence of diabetes mellitus by using the questionnaire and baseline screeningParticipants with an estimated BMD T score <−2.5 or fragility fracture in the previous 6 monthsAntibiotic intake in the previous 6 monthsSmoking and intake of alcohol >2 units per day

The following criteria are to be confirmed by the baseline questionnaire:

Participants’ intake ability and allergic reactions to probiotic and prebiotic supplementsIntake of multivitamins and mineral supplements (prescribed or over the counter), antibiotics, or use of any other medication known to affect bone metabolism and/or gut microbiotaPresence of any systemic diseaseUse of any medications such as HRT, glucocorticoids, estrogen, systemic cortisone, bisphosphonates, diuretics, antibiotics (for the gut microbiota), or other steroid hormonesActive physical activity, that is, ≥60 minutes of vigorous or moderate activity for ≥3 days.

### The Intervention: COPES-4-Bones Clinical Study

The study design is a randomized controlled trial (RCT). All the volunteer participants in the trial will undergo the following.

#### Health Questionnaire and Health Screening

##### Blood Test for the Initial Baseline Screening

Fasting blood samples will be collected at baseline for (bone biomarkers and inflammatory cytokines) routine laboratory tests as well as medical examinations to ensure that the participants are in good health. Abnormal results from this trial will be recommended for discussion with their doctors.

##### Initial Anthropometry at Baseline

The body weight of participants will be measured using a weight scale to the nearest 0.1 kg, and standing height will be measured using a stadiometer to the nearest 0.1 cm wearing light clothes and no shoes. BMI will be calculated as weight divided by height squared (kg/m²). Waist to hip ratio will be determined by measuring the waist and hip circumference to the nearest 0.1 cm using a nonstretchable tape. Other body composition measurements will be analyzed with DXA.

##### Baseline Questionnaire

The baseline questionnaire will include the following: sociodemographic, activity index and level, medications taken in the last 6 months, smoking status, and alcohol intake.

#### For Inclusion

##### Diet or Food Records

The dietary assessment of the intake of fermented milk and dairy products, including total energy, protein, minerals, and vitamin D, will be based on a 3-day diet diary. Face-to-face interviews by the principal investigator will ascertain the food record.

##### Venous Fasting

Blood, fecal, and urine samples will be collected at baseline and week 12. Blood will be collected by a phlebotomist between 8 and 10 AM after 12 hours of fasting (overnight). Table 1 shows all the variables that will be measured, rationale, and the methods to be used.

Fasting blood samples: blood samples will be collected at baseline and week 12, the end of the study, for the following:Bone metabolism markers: concentrations of serum or plasma total osteocalcin, CTx-I, total P1NP, and 25-hydroxyvitamin D will be measured using immunoassay kits and Roche Elecsys.Cartilage degradation markers: COMP precursor and CTx-II from serum will be measured.Parathyroid hormone and lipid profile tests will be measured using immunoassay kits.Inflammation markers: concentrations of inflammatory cytokines by BioLegend LEGENDplex Multi-Analyte and hs-CRP (high-sensitivity C-reactive protein) will be measured.Spot urine samples: samples of a midstream urine specimen voided spontaneously by the participants will be collected at baseline and at the end of the study and tested for protein, creatinine, and electrolyte content as well as CTx-II by ELISA (enzyme-linked immunosorbent assay).Fecal samples: samples will be collected at baseline and at the end of the study (week 12). The total genomic DNA will be extracted, and 16s ribosomal DNA will be amplified, prepped, and sequenced.

**Table 1 table1:** Study outcome measures and rationale for use.

Variables		Rationale	Methods	Baseline	Week 12

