**Methods:**

A total of 160 postmenopausal women from New Zealand will be recruited and randomized to one of four interventions or treatments for 12 weeks: control, synbiotic supplementation, exercise intervention, or synbiotic supplementation and exercise. The primary outcome measure is the bone and joint biomarkers at baseline and week 12, whereas the gut microbiota profile and inflammatory cytokine measurements will serve as the secondary outcome measures at baseline and week 12. Baseline data and exercise history will be used to assess, allocate, and stratify participants into treatment measures.

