### The Research

#### Overview

The gut microbiome could be a plausible target for the modulation of bone disorders in the aged, as it has been associated with the innate and adaptive immune system. Our previous study inquired into the association between the gut microbiome and bone health status based on the World Health Organization classification of osteoporosis among postmenopausal women [38]. The relationship between the composition and predictive function of gut microbiota in women and their bone density, classified into healthy and osteopenic or osteoporotic groups, was investigated. The findings of this recent study showed that α diversity of the microbial profiles differed based on the hip and femoral neck osteoporosis classifications. Meanwhile, β diversity principal component analysis by using the Bray-Curtis index showed differences based on femoral neck classifications. Positive correlations were observed between *Lactobacillus, Bacillus, Paenibacillus*, and *Geobacillus* (all from the phylum Firmicutes) and BMD at all sites. However, negative correlations were reported for *Bacteroides* and *Parabacteroides* and all BMD sites [39,40]. This finding agrees with previous reports that showed the importance of the *Lactobacillus* species in bone maintenance [14,41]. This result was similar to that of Li et al [42], who showed a negative correlation between *Bacteroides* and BMD.

In addition, a study conducted with ovariectomized rats showed the effects of probiotics, prebiotics, and synbiotics on mineral (calcium and phosphorus) metabolism and absorption. The effects were also observed in the form of higher *Bifidobacteria* and *Bacteroides* counts, lower pH, and reduced bone turnover. The intervention also resulted in a tendency toward lower bone alkaline phosphatase [43].

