#### Specific Aim

This study aims to examine whether supplementation of fermented milk or dairy (yogurt) with a synbiotic (probiotic+prebiotic) and weight-bearing low-impact exercise could be effective in achieving favorable changes in gut microbiota, inflammation status, and biochemical indexes of bone and joint metabolism.

Aim 1: to compare control, synbiotic, exercise, and synbiotic+exercise groups based on changes in the gut microbiota using 16S rDNA sequencing at baseline and week 12.

Aim 2: to compare control, synbiotic, exercise, and synbiotic+exercise groups based on changes in inflammation status (inflammatory cytokines) at baseline and week 12.

Aim 3: to compare control, synbiotic, exercise, and synbiotic+exercise groups based on changes in bone formation (procollagen type 1 N-terminal propeptide [P1NP]), resorption (cross-linked C-telopeptide of type 1 collagen [CTx-I]), and joint degradation (CTx-II/COMP [cartilage oligomeric matrix protein]) at baseline and week 12.

Aim 4: to compare control, synbiotic, exercise, and synbiotic+exercise groups based on changes in body composition (lean body mass and fat mass), total hip, femoral neck, and spine BMD (DXA [dual-energy x-ray absorptiometry]) at baseline and week 12.

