##### DXA Measurements

Body composition, bone mineral content, BMD, and T scores of the femoral neck, lumbar spine, and hip will be measured in participants at baseline screening.

All exercise intervention and synbiotic+exercise groups or participants will be given a wearable fitness tracker to wear during the exercise (brisk walking) of 10,000 steps. The Borg Rating of Perceived Exertion will be used to calculate intensity. Table 2 shows the interventions and dosage per participant.

**Table 2 table2:** Intervention and dose administered to participants in each group.

Intervention and treatment groups	Description	Daily intake per day
Synbiotic	Probiotic supplement Prebiotic supplement	10 billion colony forming units of *Lactobacillus sp.* 8 grams of prebiotic fiber (inulin)
Exercise	Weight-bearing exercise	10,000 steps
Placebo	Placebo	Placebo with maltodextrin

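### In the synbiotic arms, a higher Lactobacillus signal in the week-12 16S data may partly be supplement DNA and cannot by itself show a change in the resident microbiota

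*Protocol article*

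**What the plan says.** - **Exposure.** Participants are "randomized to one of four interventions or treatments for 12 weeks" (Abstract, Methods). Table 2 sets the daily probiotic in the synbiotic at "10 billion colony forming units of" *Lactobacillus sp.*, with 8 g of inulin.
- **Sampling.** For stool, "samples will be collected at baseline and at the end of the study (week 12") (Venous Fasting). No gap between the last dose and the sample is stated, and Strengths and Limitations of This Study says that follow-up cannot be extended.
- **Assay.** "The total genomic DNA will be extracted, and 16s ribosomal DNA will be amplified, prepped, and sequenced" (Venous Fasting). No strain-specific or viability step is described.
- **Use.** Aim 1 compares the four arms on "changes in the gut microbiota using 16S rDNA sequencing at baseline and week 12" (Specific Aim). The Abstract states that "the gut microbiota profile and inflammatory cytokine measurements will serve as the secondary outcome measures at baseline and week 12". Research Questions also asks whether particular microbiota changes affect bone metabolism.
- **Expectation.** The Overview reports that Lactobacillus, among other genera, correlated positively with BMD at all sites in the team's earlier work, and links this to the "importance of the *Lactobacillus* species in bone maintenance".

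**The concern.** Sequencing amplified 16S from total DNA counts bacterial DNA whatever its origin. Cells of the supplement on their way through the gut, live or dead, are counted with resident bacteria of the same genus. The genus being swallowed is also one that the background section presents as good for bone, so it is a natural candidate to be read as a beneficial shift.

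Two conclusions are exposed. First, a taxon-level comparison under Aim 1 could show more Lactobacillus in the synbiotic arms with no resident organism having changed. Second, in the analyses linking microbiota to bone, Lactobacillus abundance would partly act as a label for the randomized arm. An effect of the supplement on CTx-I by another route, such as inulin and calcium absorption (Expected Benefits or Outcomes), could then appear as an association between Lactobacillus and bone.

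**Working it through.** **The plan's own figures.** The article gives no figure for the microbiota outcome. Its sample size is consistent for dropout: 36/(1 − 0.10) = 40 per group and 4 × 40 = 160. The two synbiotic arms therefore hold 80 women at entry and 72 after the planned dropout. Nothing below depends on this.

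**What the text fixes.** Side by side: daily Lactobacillus for 12 weeks; one post-baseline stool sample at week 12; an assay of total DNA; no later sample. These together mean that supplement DNA can be in the week-12 sample and that the described assay does not identify it.

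**Illustrative mass balance.** From the document: dose D = 10^10 CFU/day (Table 2). Everything else is an outside assumption:
- native stool cells per day, T: 10^12 to 10^14
- share of the dosed DNA recovered in stool, r: 1% to 100%
- resident Lactobacillus as a share of the community, b: 0.01% to 1%
- one CFU counts as one cell, one day's dose leaves with one day's stool, and no resident organism changes

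Formulas:
- supplement share of the community: f = D·r / (T + D·r)
- apparent fold change in the genus: [b(1 − f) + f] / b
- direct Bray-Curtis shift on relative abundances: f(1 − b), which is at most f

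Example with T = 10^13, r = 10%: D·r = 10^9, so f = 10^9/(10^13 + 10^9) ≈ 0.01%. With b = 0.01%, the fold change is (0.01% × 0.9999 + 0.01%)/0.01% ≈ 2.0.

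| T (cells/day) | r | f | fold, b = 0.01% | fold, b = 0.1% | fold, b = 1% |
|---|---|---|---|---|---|
| 10^12 | 1% | 0.01% | 2.0 | 1.1 | 1.01 |
| 10^12 | 10% | 0.10% | 10.99 | 2.0 | 1.1 |
| 10^12 | 100% | 0.99% | 100.0 | 10.89 | 1.98 |
| 10^13 | 1% | 0.001% | 1.1 | 1.01 | 1.00 |
| 10^13 | 10% | 0.01% | 2.0 | 1.1 | 1.01 |
| 10^13 | 100% | 0.10% | 10.99 | 2.0 | 1.1 |
| 10^14 | 1% | 0.0001% | 1.01 | 1.00 | 1.00 |
| 10^14 | 10% | 0.001% | 1.1 | 1.01 | 1.00 |
| 10^14 | 100% | 0.01% | 2.0 | 1.1 | 1.01 |

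**A narrower set.** Assume 100–200 g of stool a day at 10^11 cells/g, so T = 1–2 × 10^13. Full recovery adds 10^10/(2 × 10^13) = 0.05% to 10^10/10^13 = 0.10%; 10% recovery adds 0.005% to 0.01%. With resident Lactobacillus at 0.01% to 0.1%, the fold change runs from (0.1 + 0.005)/0.1 = 1.05 to (0.01 + 0.10)/0.01 = 11.

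**Reading.** At genus level the artefact can be anything from negligible to large, and it is largest where resident Lactobacillus is scarce. At community level the added share never exceeds about 1%, so the direct Bray-Curtis shift is at most about 0.01, and about 0.0001 in the worked example.

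**The case against.** - **This belongs in an analysis plan.** Read filtering and taxon-level sensitivity analyses are usually specified there, and the article's Statistical Analyses section sets out no microbiota analysis. That stands for the missing filter: its absence from the article is not an error. It does not remove the point, because the dosed genus, the timing of the sample, the assay and the lack of a later sample are all fixed here, and they limit what a Lactobacillus rise can show.
- **No Lactobacillus endpoint is named.** This stands. A reader might infer that the beneficial result is built in and that a Lactobacillus rise would count as success on Aim 1. The article does not define a beneficial change by taxon and states no decision rule; the link is an inference from the Overview.
- **The community-level outcome barely moves.** This stands. A reader might infer that the whole microbiota comparison is compromised. The arithmetic does not support that for α diversity or Bray-Curtis.
- **Exposure is not confined to the synbiotic arms.** A reader might infer that all 80 synbiotic women and none of the other 80 are affected. Fermented dairy is recorded (Diet or Food Records) but not listed as an exclusion, adherence may vary, and the article does not say whether the placebo shares the yogurt vehicle mentioned under Specific Aim.
- **Filtering could discard the agent under study.** Expected Benefits or Outcomes and Synbiotics: Mechanism of Action both treat the supplemented Lactobacillus as part of the mechanism, and inulin could raise resident Lactobacillus. This stands against using only the filtered analysis or dropping the genus outright. It does not count against showing both.

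**Conclusion.** The point holds as a limit on interpretation. In the two synbiotic arms, a higher Lactobacillus genus signal at week 12 may partly reflect passing supplement DNA and cannot alone demonstrate a change in the resident microbiota. This rests on stated facts plus one assumption: that supplement DNA is still present when the stool is collected, since no washout is stated.

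The size is unknown. The 1.0- to 100-fold range, and the narrower 1.05- to 11-fold range, rest wholly on outside assumptions apart from the dose. Whole-community metrics are little affected directly. The outcome is secondary; the bone-marker primary outcome is not touched directly, and the exercise-only versus control contrast does not involve the supplement. It is worth acting on because microbiota is Aim 1, part of the principal hypothesis and the proposed route to bone.

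**What to change.** 1. For the Aim 1 taxon-level comparisons and the analyses relating microbiota change to bone metabolism, prespecify a repeat analysis with reads matching the supplemented Lactobacillus removed, or the whole genus if 16S cannot resolve it. Show it beside the unfiltered result.
2. Report the supplemented taxon separately as a marker of exposure or adherence, next to the unused-supplement record in Table 1.
3. State that modulation of the resident microbiota will not be claimed from a rise in Lactobacillus alone.

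This needs no new samples, visits or assays, only a filtering step and a second run on reads already sequenced. The drawback is that a true rise in resident Lactobacillus, for example from inulin, would show only in the unfiltered result.

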**Blood analyses**					
	OC^a^	Bone formation markers	Electrochemiluminescence immunoassay using the Roche COBAS e411 system (Roche Diagnostics)	✓^b^	✓
	P1NP^c^	Bone formation markers	Electrochemiluminescence immunoassay using the Roche COBAS e411 system (Roche Diagnostics)	✓	✓
	CTx^d^-I	Bone resorption marker	ELISA^e^	✓	✓
	25(OH)D^f^	Serum Vit D to determine the amount of circulating vitamin	Isotope-dilution liquid chromatography-tandem mass spectrometry	✓	✓
	COMP^g^	Cartilage degradation markers	ELISA	✓	✓
	CTx-II	Cartilage degradation markers	ELISA	✓	✓
	PTH^h^	To assess the regulation of serum calcium concentration	Electrochemiluminescence immunoassay using the Roche COBAS e411 system (Roche Diagnostics)	✓	✓
	Lipid profile	To assess the lipid profile	Electrochemiluminescence immunoassay using the Roche COBAS e411 system (Roche Diagnostics)	✓	✓
	Inflammatory cytokines	To assess the inflammatory status	BioLegend LEGENDplex Multi-Analyte	✓	✓
	hs-CRP^i^	To assess the inflammatory status	Electrochemiluminescence immunoassay	✓	✓
Gut microbiota data		To determine changes in the bacterial community	16s ribosomal DNA	✓	✓
Diet diary		To obtain dietary intake data	3-day diet diary	✓	✓
Exercise history record (IPAQ^j^)		For initial randomization	IPAQ	✓	✓
Baseline questionnaire (sociodemographic and medication history record)		To obtain sociodemographic status and history	Questionnaires	✓	✓
Wearable fitness tracker record		To obtain exercise regime data	Wearable fitness tracker	✓	✓
Adherence to synbiotic supplement and exercise		Documentation of unused supplements or prescribed exercise session attendance	Record keeping	✓	✓
Anthropometry		Weight, height, and waist circumference measured by a researcher at Massey University	Tanita electronic scale and stadiometer	✓	✓
DXA^k^		BMD at the total hip, femoral, neck and spine (L1-L4) and body composition	DXA using Hologic QDR series Discovery A, Bone densitometer, and Apex system software version 4.5.3	✓	✓

^a^OC: osteocalcin.

^b^Variable accessed.

^c^P1NP: procollagen type 1 N-terminal propeptide.

^d^CTx: cross-linked C-telopeptide.

^e^ELISA: enzyme-linked immunosorbent assay.

^f^25(OH)D: 25-hydroxyvitamin D.

^g^COMP: cartilage oligomeric matrix protein.

^h^PTH: parathyroid hormone.

^i^hs-CRP: high-sensitivity C-reactive protein.

^j^IPAQ: International Physical Activity Questionnaire.

^k^DXA: dual-energy x-ray absorptiometry.

##### DXA Measurements

Body composition, bone mineral content, BMD, and T scores of the femoral neck, lumbar spine, and hip will be measured in participants at baseline screening.

All exercise intervention and synbiotic+exercise groups or participants will be given a wearable fitness tracker to wear during the exercise (brisk walking) of 10,000 steps. The Borg Rating of Perceived Exertion will be used to calculate intensity. Table 2 shows the interventions and dosage per participant.

**Table 2 table2:** Intervention and dose administered to participants in each group.

Intervention and treatment groups	Description	Daily intake per day
Synbiotic	Probiotic supplement Prebiotic supplement	10 billion colony forming units of *Lactobacillus sp.* 8 grams of prebiotic fiber (inulin)
Exercise	Weight-bearing exercise	10,000 steps
Placebo	Placebo	Placebo with maltodextrin

### Statistical Analyses

G*Power statistical software version 3.1.9.7 developed in Heinrich Heine University Düsseldorf was used to calculate the sample size to ensure 95% CI with an α value of .05. We require 36 participants for each group. The within-subject SD for the primary outcome variables CTx-I and P1NP with a correlation of 0.5 was used. The number of volunteers was increased to 40 to allow for a dropout rate of 10%.

The results will be presented as either percentages or mean differences. Normality tests will be assessed through Shapiro-Wilk tests carried out on each parameter before analysis. The conventional analysis of variance (ANOVA) for RCT analysis will be used, and ANOVA for repeated measures will be applied to study treatment differences, period effect, and the interaction between treatment and period (carryover effect). IBM SPSS version 25 and Minitab statistical software version 19 (Minitab LLC) will be used for statistical analyses. Comparing groups' pretest with Mann–Whitney U test and then comparing pre- and postintervention results with Wilcoxon is one option and transforming data into ranks and performing an analysis of covariance (or ANOVA) is another option. All analyses will be considered statistically significant at *P*≤.05.

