#### Safety and Data Monitoring

The principal investigator and team will monitor the conduct, safety, and scientific integrity of the proposed clinical trial. Routine laboratory measurements, including liver and kidney function tests, blood glucose (nonfasting), and lipid profile (triglyceride, total cholesterol, high-density lipoprotein cholesterol, and low-density lipoprotein cholesterol) tests, will be performed at baseline and 12 weeks. Individuals with results that are outside the clinical range will be contacted and referred to their general practitioner. The safety precaution will be to inform all participants to report any effects of treatment, and in the unlikely event that 20% of the participants report severe diarrhea, a discontinuation of the study will be triggered. Each report will include the monitoring of compliance with informed consent and eligibility requirements, compliance with the recruitment plan according to protocol, follow-up data collection according to the protocol, expected and actual accrual, protocol violations, and patient withdrawals from the study.

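### The named two-visit repeated-measures ANOVA compares unadjusted changes in complete pairs; a baseline-adjusted primary analysis would be more precise and would resist baseline-related dropout

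*Protocol article*

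**What the plan says.** Under Statistical Analyses the article names conventional ANOVA and then states that "ANOVA for repeated measures will be applied to study treatment differences, period effect" and their interaction. If a nonparametric route is taken, two options are left open. One is a Mann-Whitney comparison of the arms at baseline followed by Wilcoxon tests of before against after. The other is analysis of covariance, or ANOVA, on ranks. No choice is made between them.

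The primary markers are measured twice, at baseline and week 12 (Specific Aim; Table 1). For the sample size, "We require 36 participants for each group" and "The number of volunteers was increased to 40 to allow for a dropout rate of 10" percent. The inputs given are an α of .05 and this: "The within-subject SD for the primary outcome variables CTx-I and P1NP with a correlation of 0.5 was used". No SD, effect size or power is stated. The Participants section confirms that "40 women aged >60 years will be recruited for each of the 4 groups".

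Table 1 has rows for adherence to the supplement and exercise and for fitness-tracker records. Safety and Data Monitoring lists, among items to be reported, "protocol violations, and patient withdrawals from the study".

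**The concern.** In a two-visit repeated-measures ANOVA, the test of whether arms change differently is the arm-by-time interaction. This is the same test as a one-way ANOVA on each woman's change from baseline. Two consequences follow from that choice.

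First, a woman without a week-12 value has no change and, unless values are filled in, leaves the analysis. Paired Wilcoxon behaves in the same way.

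Second, the change is not adjusted for baseline. A change score correlates negatively with its own starting value, because high starters tend to fall and low starters to rise. If the women missing at week 12 differ in baseline level from those who remain, and more so in one arm than another, regression to the mean appears as an arm difference. Two of the four arms walk 10,000 brisk steps a day and two do not, so uneven loss is plausible, although nothing in the article predicts it.

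At stake is the comparison of the exercise and combined arms with the others, which carries the principal hypothesis. Even if nobody is lost, precision is given away.

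**Working it through.** **The plan's own figure.** 36/(1 − 0.10) = 40.0 per arm, and 4 × 40 = 160. This reproduces. The 36 itself cannot be checked without an effect size, SD and power.

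**Inputs.** From the article: 40 per arm, two visits, correlation r = 0.5, taken here as that between baseline and week 12. Assumed: equal SD at both visits (set to 1), normal values, no true effect, loss of 20% or 30% in a walking arm against 5% in control. The article gives no loss rates by arm.

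**Precision without differential loss.**
- Variance of change: 2(1 − r) = 2 × 0.5 = 1.00.
- Variance after baseline adjustment: 1 − r² = 1 − 0.25 = 0.75.
- Ratio of standard errors: √0.75 = 0.866, so the adjusted one is about 13% smaller (equivalently, the unadjusted one is 1/0.866 = 1.15 times as large).
- In sample size: 36/0.75 = 48. Apart from one degree of freedom for the slope, 36 women per arm with adjustment do the work of 48 without it.
- The variance ratio in general is (1 + r)/2. At r = 0.3 the standard error falls by 19% (√0.65 = 0.806), and at r = 0.7 by 8% (√0.85 = 0.922).

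**Bias when loss depends on baseline.** Suppose a fraction d of an arm is lost, and always the women with the highest baseline. The mean baseline of those who remain falls by h(d) = φ(z)/(1 − d), where z is the upper d point of the normal distribution.
- h(0.05) = 0.1031/0.95 = 0.109
- h(0.20) = 0.2800/0.80 = 0.350
- h(0.30) = 0.3477/0.70 = 0.497

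The expected change given baseline is −(1 − r) × baseline, so the bias (exercise minus control) is (1 − r) × [h(exercise) − h(control)].
- 20% v 5%: 0.5 × (0.350 − 0.109) = 0.12 SD
- 30% v 5%: 0.5 × (0.497 − 0.109) = 0.19 SD

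That is the worst case. If the tendency to leave correlates only 0.5 with baseline, both figures halve, to 0.06 and 0.10 SD. The sign reverses if low-baseline women are the ones lost.

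Simulation of two-arm trials with 40 per arm agrees:

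| Baseline-related loss | Change contrast: bias; rejection at 5% | Baseline-adjusted: bias; rejection |
|---|---|---|
| Worst case, 20% v 5% | 0.12; about 9% | about 0; about 5% |
| Worst case, 30% v 5% | 0.19; 12 to 13% | about 0; about 5% |
| Correlation 0.5, 20% v 5% | 0.06; about 6% | about 0; about 5% |
| Correlation 0.5, 30% v 5% | 0.10; about 7% | about 0; about 5% |
| Equal 10% in both arms | about 0; 5 to 6% | about 0; about 5% |

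For scale, 36 v 36 gives 80% power (an assumed value) for a difference of (1.96 + 0.84) × √(2/36) = 0.66 SD. The biases of 0.06 to 0.19 SD are about 9% to 29% of that.

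**Loss completely at random.** However uneven, the bias is 0.00.

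**Bias when loss depends on response.** If leaving correlates 0.5 with an unfavourable change, the change contrast is off by 0.5 × 0.241 = 0.12 SD (20% v 5%) or 0.5 × 0.388 = 0.19 SD (30% v 5%), in favour of the arm with more loss. Adjustment multiplies this by about 0.75, leaving 0.09 and 0.15 SD. It removes about a quarter.

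**The case against.** A reader might infer that the plan drops women who stop walking or the supplement and so analyses completers by design. The article does not say that. It names no analysis set and no missing-data rule, and a condensed article commonly leaves these to the full protocol or analysis plan; that silence is not held against it. Adherence and withdrawals are recorded as separate items, and the week-12 samples are scheduled with no exemption for women who stop.

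A reader might also infer that the flat 10% allowance causes bias. It does not: it affects precision only, and its arithmetic is correct. Nor does uneven stopping bias the contrast by itself; loss must also be related to baseline or response. No text links marker level to leaving, the 20 to 30% against 5% rates are assumptions, and the 0.12 to 0.19 SD figures for baseline-related loss need every high-baseline woman to be the one lost. The population is not simply sedentary either, since the design includes a stratum with two or more high-intensity sessions a week.

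Finally, an analysis of covariance is already listed, and for response-related loss a better model helps only modestly.

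All of this stands. It does not touch the method that the article fixes. The covariance analysis appears only on ranks, as one undecided option with plain ANOVA as its alternative. The named main analysis remains an unadjusted comparison of change, and its loss of precision depends on no assumption about dropout.

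**Conclusion.** The point holds as a criticism of the primary analysis method and no further. At the stated correlation of 0.5, taken as baseline to week 12 with equal SDs, baseline adjustment cuts the standard error by about 13% whatever the dropout. If loss is both uneven and baseline-related, the named analysis could be biased by about 0.06 to 0.10 SD under moderate dependence and 0.12 to 0.19 SD at the extreme, given assumed losses of 20 to 30% against 5%. Adjustment removes this. Bias from response-related loss is only reduced, for example from 0.12 to 0.09 SD. Whether loss will be uneven or related to the markers cannot be known from the article. The dropout allowance and the 40 per arm are not in error.

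**What to change.** State that the primary analysis of each primary marker is a baseline-adjusted comparison of all randomised women in their allocated arm. There are two suitable forms:
- a likelihood model with baseline and week 12 as outcomes, a common baseline mean across arms and an arm effect at week 12, which also retains women with a baseline value only;
- ANCOVA of the week-12 value on baseline and arm, which uses women with a week-12 value and, with two visits, gives nearly the same estimate.

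Transform the marker where its distribution requires it, in place of the open choice among rank-based options. Keep repeated-measures ANOVA on complete pairs as a supplementary analysis.

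Because no model fully removes response-related bias, also confirm in the full protocol that the scheduled week-12 samples are taken from women who have stopped the intervention but remain in contact.

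The cost is a change of wording and minor extra analysis work. The visit is already scheduled and SPSS, which the article names, fits either model. The one downside to accept is that an estimate including women who stopped may be smaller than the effect in adherent women.
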